#### Secondary outcome: personality parameters

Measuring change in personality traits in the course of both dosage and therapy conditions will be done using (generalized) linear mixed models. Also the percentage of patients reaching reliable and clinically significant improvement on personality outcomes will be analyzed for both dosage and therapy conditions, using the method of Jacobson and Truax [69]. Comparison between the dosage conditions (and secondary between the therapy-conditions) will be analyzed using GEE. Finally, remission rates of personality disorders will be measured and compared for both conditions (and secondary for the therapy-conditions) with GEE at termination and follow-up (SCID-II / SCID-5-PD).

#### Economic evaluation

The economic evaluation will be conducted alongside the randomized trial, taking into account the CHEERS statement [70] and the 2015 ISPOR good research practices task force report on cost-effectiveness analysis alongside clinical trials [71]. In the economic evaluation the difference in societal costs generated by patients in the two frequency conditions (25- vs 50-sessions) will be related to the difference in clinical effects. Both a cost-effectiveness and cost-utility analysis will be performed with a time horizon of 24 months. We will consider four types of costs: (1) the costs of offering the intervention (ST or SPSP, 25 or 50 sessions), (2) costs stemming from general health care uptake besides ST / SPSP, including the costs of medication, (3) patients’ out-of-pocket expenses (e.g. traveling costs, leisure time spent on receiving care), (4) costs stemming from productivity losses due to absenteeism or reduced efficiency while at work (presenteeism). The first two types of costs will be based on the full economic costs of offering the interventions. Here, we will use the standard cost prices reported in the Dutch guideline for economic evaluation [72]. Productivity losses will be based on the gender- and age-specific labour costs, and will be estimated using the friction cost approach. Data on resource use (health care uptake) and productivity losses will be collected using the TiC-P. Medication use will be valued using prices of the Royal Dutch Society for Pharmacy. Societal costs will be related to the following effect measures in the economic evaluation: 1. Decrease in depressive symptoms over 24 months as measured with the BDI-II (cost-effectiveness analysis), 2. Quality-adjusted life-years (QALY’s) measured over 24 months, based on the Dutch tariff for the EuroQol (EQ-5D) (cost-utility analysis).

The analyses will be done according to the intention-to-treat principle. Missing cost and effect data will be imputed using multiple imputation. Incremental cost-effectiveness-ratios (ICERs) will be calculated by dividing the difference in the mean total costs between the treatment groups by the difference in mean effects between the treatment groups. Uncertainty around the ICER will be calculated using a non-parametric bootstrap approach. For each of these bootstrapped samples, the incremental costs, incremental effects, and the ICER will be calculated. The resulting ICERs will be used for further calculations and will be plotted on a cost-effectiveness plane. In addition, cost-effectiveness acceptability curves (CEACs) will be constructed to show the probability that the 50-sessions intervention is cost-effective compared to the 25-sessions intervention, as a function of willingness-to-pay per additional unit of effect (QALYs or BDI symptoms). One-way sensitivity analyses directed at uncertainty in the main cost drivers will be performed to gauge the robustness of our findings.

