## Methods/design

### Design of the study

A mono-center pragmatic randomized controlled trial with a 2 × 2 factorial design will be conducted with four parallel groups: 1) SPSP-25; 25 sessions of SPSP (*n* = 50), 2) ST-25; 25 sessions of ST (n = 50), 3) SPSP-50; 50 sessions of SPSP (n=50), 4) ST-50; 50 sessions of ST (n = 50). There is a fixed therapy duration of 9–12 months resulting in the same therapy-duration in all conditions, but different numbers of sessions and different session frequencies: in the 25-conditions once a week sessions during the first 4-6 months (16 sessions) will be followed by fortnightly sessions during the last 4-6 months (9 sessions). The 50-condition starts with a frequency of two sessions a week (32 sessions) followed by weekly sessions (18 sessions). The study follows a 2 × 2 factorial design that allows the comparison of dosage (25 vs 50 session in 1 year) in the combined therapy groups (ST + SPSP) and vice versa. The Medical Ethics Committee of VU University Amsterdam approved the study protocol (registration-number NL55916.029.15). The study is registered at the Netherlands Trial Register, part of the Dutch Cochrane Center (NTR5941).

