### Randomization and procedure

An independent research assistant will contact eligible patients within a week after intake and will invite the patient for research assessment. Additional information about the study is provided by email, giving the patient the time to consider participation. During the assessment meeting any doubts or questions about participating in the study can be discussed with the research assistant. The MINI-plus (section A and B) and the BDI-II will be assessed during research assessment and if no structured diagnostic interview has been completed during intake, the SCID-II / SCID-5-PD will be conducted. If the patient is eligible and willing to participate an informed consent is signed. Patients will then be randomized by one of two research department employees in one of four groups (with a 1:1:1:1 allocation) using a computer script performing block randomization (25 vs 50-sessions; ST vs SPSP). Randomization will be pre-stratified according to depression severity (BDI-II < =29 low, BDI-II= > 30 high). Treatment starts as soon as possible (approximately within 0 to 3 months) and patients are assigned to a therapist based on the allocated condition and the therapists availability. Patients will be assigned for the online baseline assessment in the week prior to the start of therapy. During the course of treatment patients will be requested to fill in short online assessments at 1, 2 and 3 months. At 6 months, end of treatment and follow-up extra questionnaires are added. The data collection process is monitored in detail and patients who don’t fill out the questionnaires will be reminded by the research assistant. In addition to the online measurements the SCID-II / SCID-5-PD and MINI-plus (section A and B) will be assessed at treatment termination (9–12 months) and follow-up (21–24 months) by a research assistant who is blind for condition. All data collected from interviews during research assessment at baseline, end of treatment and follow up will be entered and stored on site. Online submitted data forms are converted to the onsite database by the data analyst. All online submitted data will be checked by a research assistant on missing data or specific errors. Independent random data checks will be conducted on entry and encoding errors. All data is entered electronically. As part of the analysis, standard checks on double data entry and range checks on data values will be performed.

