Therapists are requested to fill in online assessments at 1, 2, 3 and 6 months and at treatment termination concerning the therapeutic relation, the levels of discourse in SPSP and the dominant schema modes in ST. Participants may withdraw from the study for any reason at any time. Discontinuation of the treatment can also be indicated for serious clinical reasons as concluded in consultation meetings (i.e. immediate need for hospitalization or immediate need for an additional intervention leading to considerable exceedance of the assigned psychotherapy dosage). Early discontinuation of the treatment is not a reason for withdrawal from the study: these patients will be seen for an exit-interview and will be asked to continue participating in all remaining assessments. Participants have access to post-trial care if necessary for substantial clinical reasons during follow up period. An overview of all self-report measures and semi-structured interviews is presented in Table 2. All therapist and observer ratings per assessment are presented in Table 3.

**Table 2 Tab2:** Overview of patient instruments per time point (months)

Instruments/months	I	A	0	1	2	3	6	END	FU 6 m	FU 12 m
Clinical outcomes										
Depression										
BDI-II		X	X	X	X	X	X	X	X	X
MINI plus, section A/B		X						X		X
Personality										
SIPP	X					X^a^	X	X	X	
SCID-screener	X							X		X
SCID-II / SCID-5-PD		X						X		X
YSQ-sf			X			X^b^	X	X		X
SMI			X			X^c^	X	X		X
DPI			X				X	X		X
Quality of life										
EQ-5D(5 L)			X			X	X	X		X
Happiness question			X	X	X	X	X	X	X	X
Cost-effectiveness										
Trimbos/iMTA Tic-P			X				X	X	X	X
Process/Predictors										
WAI-S				X	X	X	X	X		
Other measures										
Demografics	X									
Treatment history			X							
BSI	X		X			X	X	X		X
OQ-45	X					X	X	X		X

*I* Intake, *A* Assessment, *0* Start of therapy, *1/2/3/6* Months in therapy, *END* End of therapy (at 8–12 months), *FU 6 m* Follow-up at 6 month after end of therapy, *FU 12* Follow up at 12 months after end of therapy. ^a^SIPP subscale Relational Capacities, ^b^YSQ-sf subscales Emotional Deprivation and Failure, ^c^SMI subscales Healthy Adult, Happy Child and Detached Protector

**Table 3 Tab3:** Overview of therapist and observer instruments per time point (months)

Instruments/months	I	A	0	1	2	3	6	END	FU 6 m	FU 12 m
Process/Predictors										
WAI-S				X	X	X	X	X		
Modes/Level of discourse				X	X	X	X	X		
Other measures										
End of treatment questionnaire								X		

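### QALYs over 24 months rest on two EQ-5D points for the year after therapy, because Table 2 omits the EQ-5D at the 6-month follow-up, and the last assessment can fall short of month 24

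*Protocol article*

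**What the plan says.** Under Economic evaluation, the horizon is set for both economic analyses: "Both a cost-effectiveness and cost-utility analysis will be performed with a time horizon of 24 months". The effect measure of the cost-utility analysis is the QALY, "measured over 24 months, based on the Dutch tariff for the EuroQol (EQ-5D").

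Table 2 (Randomization and procedure) gives the collection schedule. The EQ-5D-5L row is marked at months 0, 3 and 6, at END and at FU 12 m. The cell for FU 6 m is empty and lies between two filled cells. The cost row, "Trimbos/iMTA Tic-P X X X X X", is marked at months 0 and 6, END, FU 6 m and FU 12 m. The BDI-II and the happiness item are also taken at FU 6 m.

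Timing is stated in several places:
- Design of the study: "There is a fixed therapy duration of 9–12 months".
- Randomization and procedure, text: interviews "at treatment termination (9–12 months) and follow-up (21–24 months").
- Table 2 footnote: "End of therapy (at 8–12 months"), and the last visit is "Follow up at 12 months after end of therapy".
- Objective: cost-effectiveness is to be evaluated at the one-year follow-up, with no month given.

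Missing cost and effect data are to be multiply imputed. The article gives no rule for utility between visits, or between the last visit and month 24.

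**The concern.** The article fixes both the period over which QALYs are to be measured and the visits at which utility is measured, and the two do not fit well. A visit exists halfway through the year after therapy, and symptoms and costs are recorded there, but utility is not.

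That year is where the investigators expect the higher dosage to show a sustained effect and less recurrence. An episode that begins after END and has resolved by FU 12 m can add to the costs recorded at FU 6 m while leaving the QALY unchanged. If such episodes are more frequent in one dosage arm, the QALY difference, and with it the incremental cost-effectiveness ratio and the acceptability curve, is biased.

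Multiple imputation as described does not help. The FU 6 m utility is unscheduled for every patient, so there are no observed values at that visit to impute from. Nor can an analysis plan recover a value that was never collected.

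**Working it through.** **Inputs.** Horizon 24 months (Economic evaluation). EQ-5D at 0, 3, 6, END and END + 12 months (Table 2). END at 9–12 months (text) or 8–12 months (Table 2 footnote). Months are counted from the start of therapy, as in Table 2. The documents give no utility values, so every utility figure below is an assumption.

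**Step 1: timing of the last EQ-5D.** Last EQ-5D = END + 12. With END at 9–12 this gives 21–24, which reproduces the article's own follow-up window. With END at 8–12 it gives 20–24. The unobserved tail is 24 − (END + 12) = 12 − END.

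| END (month) | Last EQ-5D (month) | Tail (months) | Tail as share of 24 | Two-point year plus tail, share of 24 |
|---|---|---|---|---|
| 8 | 20 | 4 | 16.7% | 16/24 = 66.7% |
| 9 | 21 | 3 | 12.5% | 15/24 = 62.5% |
| 12 | 24 | 0 | 0% | 12/24 = 50% |

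Month 24 is reached only when END is month 12. The schema therapy phases described under Interventions add up to 7 + 17 + 10 = 34 weeks, and 34 × 12/52 = 7.8 months. An END near month 8 is therefore compatible with that section, although the text elsewhere says 9–12.

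**Step 2: weight of each utility point.** Under linear interpolation (assumed), each EQ-5D value enters the QALY with half the length of its adjoining intervals, in years.

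| END (month) | END weight now | FU 12 m weight now | END weight with FU 6 m | FU 6 m weight | FU 12 m weight with FU 6 m |
|---|---|---|---|---|---|
| 8 | 0.583 | 0.50 | 0.333 | 0.50 | 0.25 |
| 9 | 0.625 | 0.50 | 0.375 | 0.50 | 0.25 |
| 12 | 0.750 | 0.50 | 0.500 | 0.50 | 0.25 |

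The longest gap between utility measurements is 12 months now and would be 6 months with the extra point.

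**Step 3: effect on the QALY difference.** Let d(t) be the between-arm utility difference at visit t.
- Without FU 6 m, the year contributes 0.5·d(END) + 0.5·d(FU 12).
- With FU 6 m, it contributes 0.25·d(END) + 0.5·d(FU 6) + 0.25·d(FU 12).
- The two differ by 0.5 × δ, where δ = d(FU 6) − [d(END) + d(FU 12)]/2 is the departure from the straight line.
- Assumed δ = 0.02: 0.5 × 0.02 = 0.010 QALY. Assumed δ = 0.05: 0.5 × 0.05 = 0.025 QALY.

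**Step 4: the tail.** If an assumed utility difference of 0.02–0.05 is carried to month 24, it adds 0.02 × 3/12 = 0.005 to 0.05 × 3/12 = 0.0125 QALY over 3 months. Over 4 months it adds 0.02 × 4/12 = 0.007 to 0.05 × 4/12 = 0.017 QALY.

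**The case against.** The strongest reply is that QALYs remain computable from five time points, that the affected analysis is secondary, and that some conclusions a reader might draw go further than the documents allow. Much of this stands.

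- *Relapse after therapy is invisible.* A relapse still present at FU 12 m is captured by the EQ-5D there. Only changes that arise and resolve between END and FU 12 m are missed, and they bias the comparison only if they differ between arms. Maintenance of the depression effect is covered by the BDI-II at both follow-ups and the MINI-plus at the last one.
- *The plan prescribes a straight line.* It states no interpolation rule. Linear interpolation is assumed here, and the rule may sit in an analysis plan that is not shown.
- *The error could be 0.05 QALY or more.* That needs a departure of 0.10. If the trial's d = 0.45 applied to utility with an assumed SD of 0.20–0.30, the whole effect would be 0.45 × 0.20 = 0.09 to 0.45 × 0.30 = 0.135. A departure of 0.10 would be about as large as the whole effect, which is extreme.
- *The short horizon favours one arm.* Therapy duration is meant to be equal across conditions, and patients who stop early are asked to continue with assessments. No difference between arms is shown. The Objective section already ties cost-effectiveness to the one-year follow-up, so 24 months may be a nominal length.
- *Costs and utility must share dates.* They need not. Resource use accumulates over periods and utility is sampled at points. The EQ-5D also has a month-3 value that the TiC-P lacks.
- *The QALY difference is unadjusted for baseline.* The phrase "by the difference in mean effects between the treatment groups" defines a ratio and does not exclude adjusted means. Chance imbalance in baseline utility is imprecision that the planned bootstrap already carries.

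The reply does not remove the empty EQ-5D cell at FU 6 m, or the disagreement between the timing and horizon statements.

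**Conclusion.** The point holds as a limited weakness in the cost-utility part of the secondary economic evaluation. The primary depression analyses are untouched, and the BDI-II-based cost-effectiveness analysis has its FU 6 m value.

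Two facts rest on the document alone. First, utility over the 12 months after therapy, half of the stated horizon, is measured only at its two ends. Second, for patients ending therapy before month 12, up to 3 months (text) or 4 months (Table 2 footnote) of the 24 are unobserved.

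The size of the first depends on two assumptions, linear interpolation and the departure at FU 6 m. With a departure of 0.02–0.05, the QALY difference is off by 0.010–0.025. The second is largely a matter of consistent definition, with no shown difference between arms. The change is worth making because it is cheap, recruitment is still open according to Trial status, and the omitted values cannot be recovered later.

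**What to change.** 1. Add the EQ-5D-5L to the existing online FU 6 m assessment for all patients who have not yet passed it. The cost is five extra items and a small amendment. Patients already past that visit will have no FU 6 m value, and the analysis must say how they are handled. Once other patients have observed values at that visit, multiple imputation has something to work from.
2. Compute QALYs and costs on actual assessment dates, and state how utility is interpolated between visits. This costs only analysis wording.
3. Reconcile the timing of END (8–12 months in the table footnotes, 9–12 in the text) and the horizon (24 months under Economic evaluation, one-year follow-up under Objective). One option is to define the horizon as the FU 12 m assessment. If 24 months is kept, add a rule for the time between the last assessment and month 24.
4. Optionally, adjust the QALY difference for the EQ-5D already collected at month 0. This is a gain in precision, not the correction of an error.

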### Drop out analysis

Treatment dropout rates will be compared between conditions using survival analysis.

### Analysis of moderators and mechanisms of change

To identify mechanisms of change and the strength of the factors involved, both multilevel mediation models and structural equation models will be used. Mixed regression analysis will be used to analyze the moderating effect of type of therapy (SPSP/ST) on outcome.

## Discussion

In this article the design of a pragmatic randomized clinical trial comparing two psychotherapy dosages is presented in a sample of patients with both depression and PD. This study is the first to investigate the effect of therapy dosage in this specific co-morbid patient group. If this study would show 50 sessions to be more effective than 25 sessions in treating depression and preventing relapse, this implies better and more enduring treatment results, less patient suffering and a reduction of societal and health care costs. An important additional aim of this study is to test a potential differential effect on improvement of personality characteristics between dosages. If the 50 sessions condition would lead to a more healthy development of personality characteristics, this could have protective value against relapse of depression. In addition, this study will contribute to the scarce evidence available on integrated therapies such as SPSP and ST in treating patients suffering from both depression and PD.

A long standing and poorly resolved important clinical question in psychotherapy is ‘what works for whom and why’. By addressing several pretreatment predictors, moderators and process factors we hope this study contributes to this question. Also, differential predictive factors may be found in ST and SPSP, by measuring both specific and non-specific treatment factors. However, single studies are generally underpowered to develop reliable prediction models. Combining data of studies in Individual Participant Meta-analyses is now recognized as a gold standard approach in prediction modeling research [73]. By gathering all data reliable and fully transparent we think this study may contribute to create this kind of joint analyses of data. In future this will allow us to select better optimal treatments for individual patients and shed more light on working mechanisms in psychotherapy.

Generalization of results from RCT designs are criticized because of, among other things, their limited inclusion and the often rigid conductance of therapies. In addition, we expected problems with acceptance by this complex patient sample of measurements at each session, and therefore a possible increase in the risk of dropout and a reduction of the generalizability of the study as a whole, limiting its value for daily clinical practice. This RCT is conducted in an ecologically valid environment of complex secondary care patients. We tried to make inclusion criteria as broad as possible. We will check for a good therapy reliance but both protocols allow a certain flexibility to adjust it to individual needs of the patients. They are not conducted according to a session by session description, as both treatment protocols prescribe adaptation of the focus of treatment and techniques to the momentary state of the patient. We hope this may facilitate participation and moderate dropout during therapy, which normally is relatively high in this kind of complex patient samples. Nevertheless, studying dosages makes it inevitable to apply a fixed number of sessions and session frequency. In clinical practice dosage might be applied with more flexibility depending on the course of therapy. Therefore, we think it would be helpful to complement data derived from this RCT by observational studies to accomplish a well-balanced evidence for clinical practice.

A strength of this study is the fact that patients are randomized over both dosage and type of therapy. This provides the opportunity to compare differences between both dosages in the larger samples of the combined therapy groups and vice versa. In addition, the large amount and broad range of both self-report and observer-rated measures of depression, personality, psychodynamic measures, and moderators and mediators are a strength of the study. Also, the frequent assessments on multiple time-points during therapy could give us the opportunity to detect temporal relationships that may shed light on working mechanisms. Moreover, an additional strength of this study is that it includes researchers with allegiance to both ST and SPSP, reducing the potential effects of researcher allegiance on treatment outcome. Finally, the economic evaluation is a strength of this study as it can gather insight in the effect of dosage on several aspects of costs.

The trial has several limitations that should be considered in evaluating the results. The first limitation of this study is the absence of a treatment as usual (TAU)- or waiting list condition. Since both conditions were adapted forms of existing therapies and were tailored for this subgroup of comorbidity, they have not been tested before in this form. However, we are dealing with a complex group of patients, almost all of whom have been treated earlier with little success, usually with therapies such as PST, CBT or IPT that are widely available in the Netherlands, and/or in combination with antidepressants. This made it difficult to find a feasible and acceptable TAU condition. In addition, all the patients were referred for specialized treatment, which, from a patient’s perspective, makes a prolonged stay on a waiting list unacceptable. As the duration of all the treatments is 1 year, we also considered it inappropriate to include a waiting list condition for the eligible patients. Instead, we chose to offer two specialized treatments focusing on depression in relation to underlying personality pathology. In addition, the main research question is the effect of a higher dosage of treatment. The 25 condition may therefore in effect be considered as a control condition. The effectiveness of both therapies in broad groups of depressed patients has been demonstrated [18, 74], in the case of PDT normally in 15–20 sessions and in the case of SFT in 32 sessions. We therefore chose the 25 condition as the minimum dosage required to be effective.

Secondly, one might question whether the two treatments are really different in daily practice. In general, common factors in the treatments, and in particular the therapeutic relationship, have been shown to be the most relevant working mechanisms for psychotherapy (e.g. [75]) and both therapies involve a search for underlying patterns related to the depression. Nevertheless, in practice, we think the approaches are perceptibly different at the level of applied concepts and techniques. In SFT, this difference is seen in the schemas and modes with the distinctive feature, in SPSP being the levels of discourse used to gain insight. Interventions such as diagnostic imaginations and experiential techniques such as role play and imagery rescripting are applied in SFT, while SPSP is a more open and exploratory discussion with the patient conducted in order to acquire an insight into the background of depression from an interpersonal and intrapersonal perspective. We therefore expect a difference in approach to be perceptible for both therapists and patients. This is also checked in the adherence part of the study.

The scope of this study does not allow for a full check of the differences between SPSP and SFT in terms of outcome. However, potential differences related in particular to the aims of the interventions could be analyzed at an exploratory level using secondary personality outcome measures. Outcome measures were therefore not only related to DSM-5 categories of personality disorders (SCID-PD) but also to both psychodynamic (SIIP-118, DPI) and schema therapy (YSQ-sf, SMI) concepts.

Thirdly, we used wide eligibility criteria in an attempt to select a sample which is representative for the general group of patients with depression and PD. Nevertheless, all patients included in the trial were referred to a center for PD assuming that the less severe and less enduringly depressed patients with PD might be missed out in the trial as they are treated at centers specialized in depression. Also, depression severity is used as the main outcome measure, even though this comorbid patient group has more psychological complaints than only depressive symptoms.

Fourthly, categorical DSM diagnoses were used to measure the inclusion criteria for both depression and PD. Thus nearly legitimate patients were excluded which, in view of the dimensional distribution in the real world of both severity personality pathology and of depressive symptoms, limits the generalization of the study.

Also, the dosage conditions of 25 or 50 sessions were chosen arbitrary and although these dosages can be considered as adequate for treating depression, the dosage is considered to be relatively low for treating PD. If both 25 and 50 sessions would not be sufficient to treat depression in this co-morbid patient group, it could be falsely interpreted that, without clear differences between the groups, the less intensive and less expensive 25 sessions condition would be preferred. Instead, effect sizes must be taken into account and additional research might be necessary to investigate whether higher dosages will lead to better outcomes.

The current study cannot distinguish between session frequency and total amount of sessions because the therapy duration was set to 1 year in all conditions. Thus, in case of significant differences in favor of the 50 sessions, follow-up studies are needed to disentangle the contribution of the number of sessions from the frequency effects.

A last limitation of the study is the fact that it is not powered to detect a clinically relevant difference between SPSP and ST if this would be smaller than d = .45. Even if the study would be powered to be able to detect a difference smaller than d = 0.45, we would not expect a difference between SPSP and ST. However, the study sample is not large enough and therefore underpowered to demonstrate equivalence between both theoretical treatment orientations.

This study aims to contribute to the evidence on psychotherapy for patients with co-occurring depression and personality disorders. Furthermore, this is the first study to compare two psychotherapy-dosages in this comorbid patient group. This study can help to get insight in how frequent and how much psychotherapy is needed to treat these complex patients. And finally, we hope this study will help to understand some of the processes that account for therapeutic changes.

